## Aim 1: Evaluate the impact of the ACP-GV National Program on the proportion of ACP discussions in VHA by comparing ACP-GV sites to propensity score-matched control sites not implementing ACP-GV

### Design

The 35 ACP-GV sites will be considered “intervention” sites. We will identify a set of matched “control” sites (*N* = 35) defined as VHA facilities not implementing ACP-GV based on an analysis of the ACP-GV workload specific code in VA Corporate Data Warehouse data and not participating in the National Program implementation activities but documenting ACP discussions as noted in the VA Corporate Data Warehouse and using AD note titles. Our hypothesis is that ACP-GV sites (i.e., intervention sites) will have a higher proportion and significantly greater quarterly and annual rates of ACP discussions compared to the PS-matched control sites. Given that the sites were not randomized to either the intervention or control, we will use PS matching to create a “pseudo” randomized evaluation design. The PS is a model-based conditional probability of a site’s membership in the intervention, given its observed site characteristics [21]. We will use a logit model to estimate the PS for each site. The dependent variable of the logistic regression model is being/not being in the ACP-GV intervention group. The independent variables are site characteristics including: rurality, geographic location, Veterans Integrated Service Network (VISN), staffing, facility size, and aggregate veteran demographics such as age, gender, and race/ethnicity. We will use a greedy matching algorithm based on 5-to-1 digit matching [22]. An initial ACP-GV site will be randomly selected from the existing sites to start the process. A non-ACP-GV site (i.e., control) with the closest PS that lies within a fixed distance will be selected for matching. If multiple control sites have PS that are equally close, then one of the control sites will be selected at random. The process will continue until all ACP-GV sites that can be matched have been matched. To evaluate the success of the PS matching, we will compare the balance in the distributions of all the observed site covariates between the two groups using standardized difference plots. An absolute standardized difference of less than 10% suggests a negligible imbalance between the two groups for a given site covariate [23]. A PS matching limitation is if no control sites have PS that lie within the predefined distance (i.e., caliper) of an intervention site, then that ACP-GV site is not included in the PS-matched sample. Given sample size limits, if the PS matching produces a limited number of pair matches, we will consider other strategies, (e.g., PS through stratification, covariate adjustment with PS, or inverse PS weighting).

### Data analysis for aim 1

We will aggregate patient-level outcomes of the ACP discussions and site characteristics (e.g., geographic location, facility size, rurality, etc.) across VHA sites quarterly and annually for descriptive purposes, and then compare the proportion of ACP discussions with the PS-matched control sites. We will specifically examine sites with a high annual rate of ACP discussion and low ACP-GV rates and vice versa to identify patterns and trends. We will present numerical variables as means (SD) or medians (interquartile-range) and categorical variables as counts and percentages (with 95% confidence interval). We will use a significance level of 0.05. To compare annual rates of ACP discussions, the primary outcome for this aim, we will use a two-sided *z*-test with pooled variance to test the difference in proportions across the two groups (i.e., ACP-GV vs. non-ACP-GV). As a secondary analysis, multivariable Poisson regression will examine the differences in annual rates of ACP discussions, while accounting for potential imbalance in site characteristics. Given the sample size, we will build a parsimonious model based on forward model selection.

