### Why do ACP in healthcare settings?

The lack of ACP discussions increases the risk that veterans will receive care different from what they prefer and may experience unnecessary interventions leading to increased suffering and higher health care costs [4, 5]. While VHA Handbook 1004.02 mandates personalized ACP discussions including information on AD for all patients in all VHA settings to comply with the Patient Self-Determination Act of 1990 and the Joint Commission, documentation of these discussions in VHA is challenging. This may be due to patient and provider barriers, such as a lack of veteran awareness and lack of perceived clinical priority by providers, respectively [6]. Also, in our clinical experience [7–9], ADs of VHA patients are difficult to quantify using electronic health records or administrative data retrieval systems since they are scanned or hard copy documents. Given these barriers, a new data architecture system launched in FY 20 will provide a national view of ADs across the VHA. Future studies will compare the VA to the community AD completion rate of 26% [10], yet current estimates using this community rate note that 6.7 of the 9.05 million enrolled veterans do not have an AD and may be hospitalized without their medical preferences being known.

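### Aim 1 requires control sites, but not ACP-GV sites, to document ACP discussions under AD note titles, the source of the outcome; this can understate the programme effect by an unknown, possibly nil, amount

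*Protocol article*

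**What the plan says.** All references are to the Protocol article.

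- **Intervention group (Aim 1, Design):** "The 35 ACP-GV sites will be considered “intervention” sites". No further condition is attached to them in aim 1.
- **Control group (same section):** facilities without the ACP-GV workload code that are also "not participating in the National Program implementation activities but documenting ACP discussions as noted in the VA Corporate Data Warehouse and using AD note titles". No threshold and no period are given.
- **Outcome (Data analysis for aim 1):** "To compare annual rates of ACP discussions, the primary outcome for this aim", followed by "we will use a two-sided *z*-test with pooled variance to test the difference in proportions across the two groups".
- **Source of the outcome (Data sources; Data collection for aims 1 and 2):** the Corporate Data Warehouse, including AD note titles and the ACP-GV workload code. Controls by definition lack the workload code, so note titles are the only marker of a discussion that the article names for them.
- **Propensity score covariates (Aim 1, Design):** rurality, location, VISN, staffing, facility size and aggregate veteran demographics. Earlier ACP documentation is not listed.
- **Context (Why do ACP in healthcare settings?):** a VHA handbook mandates ACP discussions in all settings, yet "documentation of these discussions in VHA is challenging".

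**The concern.** Two of the three control conditions describe absence of exposure. The third is a condition on the documentation that produces the outcome, and it is placed on one group only.

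Take two facilities that do not use the AD note titles. One joins ACP-GV, whose audit-and-feedback strategy (Table 1) promotes a documentation process, and so begins to use them; it is counted. The other does not join, carries on as before, and is excluded from the control pool. If such facilities exist, the controls that remain have a higher average rate than non-participating facilities as a whole, and the comparison drifts from ACP-GV versus no ACP-GV towards ACP-GV versus facilities that document.

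Neither the matching nor the planned balance check on site covariates would reveal this, because prior documentation is not among the listed covariates. At stake is an understated effect, or a false null, in an evaluation meant to inform spread of the programme across VHA.

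**Working it through.** **1. No figure to reproduce.** The article gives no expected rates, effect size or power for aim 1. The site counts agree: 23 funded + 12 unfunded = 35.

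**2. Candidate controls.** About 170 facilities (Sample) − 35 = about 135.

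**3. Effect of the rule if non-documenting facilities are true zeros.** Let f be the share of the 135 with no documented discussions and r the mean rate in the rest. Without the rule the control mean is (1 − f)r; with it, r. The control rate is therefore multiplied by 1/(1 − f), and the observed rate ratio is the true ratio × (1 − f).

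**4. Effect of removing the rule if those zeros are uncaptured discussions.** If these facilities in fact have rate r but are recorded as 0%, the control mean falls from r to (1 − f)r. The observed ratio is then the true ratio ÷ (1 − f).

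Assumptions, none of them from the article: f as shown, a true ratio of 1.20, sites of equal size, f unrelated to the propensity score, and outcomes captured at every ACP-GV site.

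| f | Facilities (135 × f) | Control multiplier 1/(1 − f) | Observed ratio: rule kept for controls only, true zeros | Observed ratio: rule dropped, uncaptured zeros |
|---|---|---|---|---|
| 0 | 0 | 1.00 | 1.20 | 1.20 |
| 2% | 2.7 | 1.02 | 1.18 | 1.22 |
| 5% | 6.8 | 1.05 | 1.14 | 1.26 |
| 10% | 13.5 | 1.11 | 1.08 | 1.33 |
| 20% | 27 | 1.25 | 0.96 | 1.50 |

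The last two columns move in opposite directions. A control-only filter can hide an effect; having no filter can exaggerate one.

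**5. Which kind of zero is more plausible?** 9.05 million veterans / 170 facilities is about 53,000 per facility. At a documentation rate of only 0.1%, and assuming independence, the chance of no note at all is (1 − 0.001)^53,000, about 10⁻²³. At a facility of average size, a zero would thus point to non-use of the note titles, not to a low rate by chance. That favours keeping a capture filter. It does not justify applying the filter to one group.

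**6. Does anything else in the article impose the condition on ACP-GV sites?** Data collection for aims 1 and 2 dates a site's start by its first use of the workload code and the AD discussion note. That rule allocates aim 3 costs to periods and is not an aim 1 entry criterion. A site can also meet it by joining the programme, so it says nothing about documentation beforehand.

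**The case against.** The strongest case for the plan is that the clause is a measurability check. The outcome is read from note titles, so a facility that does not use them has a missing rate, not a rate of zero. This stands, and it is why the condition should not simply be removed.

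Several further points also stand, at least in part:

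- With no threshold stated, the literal rule removes only facilities with no documentation. The article does not show that any exist, and the mandate suggests few.
- The remark that documentation is challenging is explained there by patient and provider barriers. That fits incomplete recording within facilities better than whole facilities that never use the titles.
- ACP-GV sites that have started probably use the AD discussion note in the outcome year, so the groups may differ little in practice.
- Any bias from the rule works against the stated hypothesis. It could mask a benefit but not create one.
- A condensed article may leave a threshold and look-back period to a fuller document.

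What does not fall away is the asymmetry, because it is in the stated definitions themselves. A measurability check serves its purpose only if it is applied to both groups and judged before exposure.

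**Conclusion.** The point holds as a one-sided eligibility condition on the source of the outcome, which the listed matching covariates do not address. Its consequence is conditional: if some non-participating facilities do not use the AD note titles, the rule can raise the control rate and understate the programme effect. The multiplier 1/(1 − f) runs from 1.00 at f = 0 to 1.25 at f = 20%, with f wholly assumed. The actual bias may be nil.

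A reader might infer more: that the control group is in fact enriched on the outcome, that controls must have been documenting beforehand, or that a large part of the effect will be lost. The article supports none of these. It gives no count of non-documenting facilities, no period for the condition, and no rates from which a loss could be calculated. The change is still worth making, because the asymmetry is plain in the text and cheap to remove.

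**What to change.** In the Design section of aim 1:

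1. Keep documentation under AD note titles as a data-capture filter, state what counts as documenting, and apply it identically to ACP-GV and control facilities.
2. Judge it in a common period before the ACP-GV sites' start, never in the outcome year.
3. Report how many facilities it removes from each group.
4. Add a sensitivity analysis that retains all 35 ACP-GV sites.

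The cost is a few sentences and an additional run on warehouse data of the kind already planned, provided that note titles can be retrieved for the earlier period. The downside is that a few ACP-GV sites without prior documentation may leave the primary matched comparison, which is already small; the sensitivity analysis shows whether that matters.

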To complete aims 1 and 2, we will use VHA administrative date from the VA Corporate Data Warehouse data to create patient, clinic, facility, and site-level variables, including veteran demographics, service utilization, AD note titles, and ACP-GV workload. For aim 2, we will merge this data with site-level variables from the ACP-GV Implementation Team Site Tracking Reports, which include sites with funded FTEE and an estimate of the unfunded sites staffing patterns. We will then add to the above data collected on the ACP-GV sites’ participation in the implementation activities from the ACP-GV Implementation Team’s Site Tracking Reports.

For aim 3, we will develop protocols with the ACP-GV Implementation Team to collect new data using an adapted version of the Time Tracking Tool developed by the Behavioral Health Team Based QUERI [20], which will quantify and connect the amount of time each staff member spends in implementation activities to allow for analysis of each strategy alone or in combination. Because implementation costs will be obtained from sites at varying stages of implementation, we will define the index date of transition from pre-implementation to implementation for an individual site as the date of initial use of the ACP-GV-specific workload code and AD discussion note by that site, while sustainability will be assessed using data for the 12 months following the index date when they started implementing ACP-GV. We will reconcile this time tracking data by allocating each cost to a site-specific period (i.e., pre-implementation, implementation, or maintenance) relative to the site-specific index date to use as implementation cost data for aim 3.

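### Aim 1 names no pre-program ACP discussion rate in matching, balance check or analysis, so any prior difference left after matching would be read as program effect

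*Protocol article*

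**What the plan says.** The Aim 1 Design section acknowledges the allocation problem and relies on matching to solve it: "Given that the sites were not randomized to either the intervention or control, we will use PS matching to create a “pseudo” randomized evaluation design". Of the score it says: "The independent variables are site characteristics including: rurality, geographic location, Veterans Integrated Service Network (VISN), staffing, facility size, and aggregate veteran demographics"; age, gender and race/ethnicity are given as examples of the demographics. Matching success is judged by standardized differences on the observed site covariates. If too few pairs form, the alternatives are stratification, covariate adjustment or weighting, all based on the propensity score.

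The section on data analysis for Aim 1 plans to aggregate outcomes by site and then "compare the proportion of ACP discussions with the PS-matched control sites". For the primary outcome, the annual rate, "we will use a two-sided *z*-test with pooled variance to test the difference in proportions across the two groups". The level is fixed: "We will use a significance level of 0.05". As the secondary analysis, "multivariable Poisson regression will examine the differences in annual rates of ACP discussions, while accounting for potential imbalance in site characteristics", with forward selection.

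Two other sections matter. Data sources says the tracking report follows any facility that shows interest or applies, so entry is by the site's own choice. Aim 3 compares ACP costs in the year before with the year after a site joined. The data collection section, in its Aim 3 paragraph, defines a site-specific index date: "as the date of initial use of the ACP-GV-specific workload code and AD discussion note by that site".

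**The concern.** A facility's interest in an ACP program may well go with how much ACP it already does, and geography, size and demographics need not capture that. The earlier discussion rate is the most obvious predictor of the later one. Without it, Aim 1 cannot separate a program that changed discussion rates from sites whose rates already differed when they joined. The Aim 1 heading promises an evaluation of the program's impact, so this is its central inference. The article does plan a before/after contrast, but only for costs.

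**Working it through.** **No plan figure to reproduce.** The article gives no power, effect size or between-site SD. The only arithmetic that can be checked, 23 funded + 12 unfunded = 35 sites, is correct.

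**Where a baseline rate could enter Aim 1**

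| Step | What is named | Pre-program rate named? |
|---|---|---|
| Propensity score | rurality, location, VISN, staffing, size, demographics | no |
| Balance check | observed site covariates | no |
| Primary test | annual rates, two groups, pooled z-test | no |
| Secondary model | Poisson, site characteristics (examples: location, size, rurality) | no |
| Fallbacks | other uses of the propensity score | no |

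**Illustration 1: site-level test, no program effect.** Inputs: 35 sites per group and two-sided alpha 0.05 (Aim 1); residual gap b in units of between-site SD (assumed, 0.2 to 0.5).

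SE = sqrt(2/35) = 0.239 SD, treating the groups as independent. 
P(reject) = Φ(b/SE − 1.96) + Φ(−b/SE − 1.96).

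- b = 0.2: b/SE = 0.84, P = 0.13
- b = 0.3: b/SE = 1.25, P = 0.24
- b = 0.5: b/SE = 2.09, P = 0.55

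**Illustration 2: simulation, no program effect.** Assumed: 35 v 35 sites, mean rate 10% or 20%, SD of stable site levels 3 to 5 points, year-to-year correlation 0.8, 2,000 runs per setting.

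| Pre-existing gap (points) | Post-only estimate | Post-only site-level rejection | Estimate from change | Rejection from change |
|---|---|---|---|---|
| 1 | about 1.0 | 11–25% | about 0 | 5% |
| 2 | about 2.0 | 30–68% | about 0 | 5% |
| 3 | about 3.0 | 59–95% | about 0 | 4–5% |

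The gap passes one-for-one into the estimated effect. Change from baseline removes it here because the simulated gap is stable over time. Regression on one baseline year with correlation 0.8 would leave 1 − 0.8 = 20% of the gap (0.4 of 2 points), and matching on that rate behaves similarly. Neither method is free of assumptions, but both remove most of what the post-only comparison keeps.

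**Precision.** Adjusting for a baseline with correlation r multiplies the SE by sqrt(1 − r²). With r = 0.7 this is 0.71, and with r = 0.9 it is 0.44 (both assumed), a reduction of 29% to 56%.

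Both illustrations use a site-level test on purpose. The planned pooled z-test raises a separate question about clustering by site, which is not counted here.

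**The case against.** The covariate list is introduced as examples, and the data collection section lists service utilization and AD note titles among the variables to be built for Aims 1 and 2. A prior rate is therefore not excluded, and a condensed article may leave the final list to a fuller plan. That stands as a limit on wording: the rate is not named, which is different from being ruled out. It does not answer the point, because the article goes as far as stating the balance check, both models and the fallbacks, and no change or baseline adjustment appears in any of them.

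The assumed gap must survive matching on the listed covariates, and low-rate sites could apply as readily as high-rate ones. That also stands, so the direction is open. The article also openly calls itself observational.

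A usable baseline may not exist everywhere. The index date is tied to first use of the AD discussion note, so some sites may have no such note beforehand. A zero baseline would then turn adoption of a note title into apparent effect. This stands and shapes the fix.

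Three stronger readings are tempting but not supported:

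- **Staffing as a post-treatment covariate.** The article does not say when Aim 1 staffing is measured, and it merges funded FTEE from the tracking reports for Aim 2.
- **Control eligibility conditioning on the outcome.** Controls must be "documenting ACP discussions as noted in the VA Corporate Data Warehouse and using AD note titles", but this sets no level, and such discussions are mandated in all VHA settings.
- **Mid-year starts diluting the annual rate.** No outcome window is stated for Aim 1, no site is said to have started mid-year, and the remark about varying stages of implementation concerns costs.

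**Conclusion.** The point holds in this form: as written, Aim 1 has no named protection against differences in ACP discussion rates that existed before sites joined and that remain after matching. Any such residual would pass in full into the estimated effect. Its size and sign cannot be known from the document. The 13%, 24% and 55% rejection rates rest on assumed residual gaps of 0.2, 0.3 and 0.5 SD, and the simulation on an assumed site SD and year-to-year correlation. A reader should not infer that ACP-GV sites did have higher rates beforehand, or that the result must favor the program. The defect lies in the method the article fixes for its impact aim, and a better one is available from the same data source.

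**What to change.** 1. From the Corporate Data Warehouse AD note titles, compute each ACP-GV site's ACP discussion rate for the year before it joined, and the rate of its matched control for the same calendar period. Because the score is fitted before pairs exist, compute candidate controls' rates for each joining period, or match within joining periods.
2. Add this rate to the propensity score and to the standardized-difference check.
3. Analyse at site level, either with adjustment for the pre-program rate or as a matched difference-in-differences. Name one as primary in advance, since they rest on different assumptions, and report the other.
4. State that the matching covariates, including staffing, are measured in that pre-program period.
5. For sites with no AD discussion note in use before their index date, define a shorter or alternative baseline (for example, any AD note title), and repeat the analysis without these sites.

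The cost is a longer pull from the same warehouse and revised wording. The main drawback is the subset without a valid baseline: excluding them reduces an already small sample, and a substitute baseline measures something slightly different.

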## Aim 2: Among ACP-GV sites, document and compare ORH-funded and DEI-unfunded sites on the effectiveness of implementation strategies (individual and combinations) used by sites in the ACP-GV National Program on ACP discussion and AD completion rates across the VHA

### Data analysis for aim 2

We will use a comparative case study approach to compare funded sites to unfunded sites on the two outcomes of ACP discussion and AD completion rates for aim 2. Due to the small number of sites, we are hindered in our ability to control for confounders. Yet, we anticipate that additional funding for staff positions will largely impact outcomes. Therefore, we will track the other four implementation strategies (see Table 1) to serve as mediators of impact. If funding expresses greater participation in the other strategies, then there may be a mechanism of action within accessing new funding alone, or because it is in combination with the other strategies.

In our preliminary data, there is some evidence of variation in participation in the implementation strategy of ongoing training by funded sites and increased uptake of ACP-GV vs. unfunded sites. We will use the Implementation Team Site Tracking Report and qualitative interviews from aim 3 and aim 4 to determine if we can make quantitative inferences as to what funding imbues and what impact it has on the other implementation strategies. To provide feedback to our partners for quality improvement and to not lose important trends that may exist in the data that may help understand larger trajectories of change, we will generate quarterly reports tabulating the number and type of implementation strategies used at each site per quarter and the extent to which each of the sites achieved the implementation outcomes. The annual summative evaluation report will describe the implementation strategies that were used by multiple facilities which were most successful and least successful in achieving positive outcomes. These quarterly briefs, annual reports, and our aim 4 analyses will be synthesized to support sustainability and spread of the initiative.

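### Aim 2 compares funded and unfunded sites on unadjusted rates and cites the small number of sites, although the patient demographics already extracted would allow case-mix standardisation

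*Protocol article*

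**What the plan says.** All references are to the protocol article.

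- **Data collection for aims 1 and 2.** Data Warehouse records will be used "to create patient, clinic, facility, and site-level variables, including veteran demographics, service utilization, AD note titles, and ACP-GV workload". This extract serves both aims.
- **Aim 1, Design.** The site characteristics in the propensity score model include "aggregate veteran demographics such as age, gender, and race/ethnicity". Balance is then judged covariate by covariate: "An absolute standardized difference of less than 10% suggests a negligible imbalance between the two groups for a given site covariate". If few pairs match, the fallbacks named are "PS through stratification, covariate adjustment with PS, or inverse PS weighting", all of which still work at site level.
- **Data analysis for aim 1.** Individual outcomes are first rolled up to site, by quarter and by year: "We will aggregate patient-level outcomes of the ACP discussions and site characteristics". The primary test of annual discussion rates is a "two-sided *z*-test with pooled variance to test the difference in proportions across the two groups". A secondary Poisson regression accounts for imbalance in site characteristics, with forward selection.
- **Data analysis for aim 2.** Funded and unfunded sites are compared on ACP discussion and AD completion rates by a comparative case study. No matching, weighting or adjustment is named. The stated reason is: "Due to the small number of sites, we are hindered in our ability to control for confounders".
- **Sample.** There are 23 funded and 12 unfunded sites, 35 in all. The Data sources section says the funding goes to rural sites.

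**The concern.** Aim 2 carries the project's main evaluation question, the effect of funding staff positions. If the chance of an ACP discussion or a completed AD varies with age, sex or race/ethnicity, and funded and unfunded sites serve different mixes of veterans, their crude rates will differ even when funding does nothing. Funding follows rurality, so the two groups of sites need not be alike. The documents do not report whether their demographic mix differs.

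The plan treats limited control of confounding as a consequence of having 35 sites. That is right for covariates that vary only between sites: a 23 v 12 comparison supports very few of them. It is not right for patient demographics. The relation between age and having a discussion is estimated from veterans within sites, and the standardised site rates that result enter the same 23 v 12 comparison in place of the crude ones. The plan thus presents as unavoidable a bias that data already in hand could reduce. The aim 2 results feed an annual report on which strategies succeeded most and least.

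**Working it through.** The plan states no power, detectable difference, discussion rate or between-site variance, so it has no figure of its own to reproduce beyond 23 + 12 = 35, which agrees. Everything marked *assumed* below is illustrative.

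**1. Is there patient-level information to use?** 9.05 million veterans over about 170 facilities is 9,050,000 / 170 ≈ 53,200 per site, assuming equal size. Age-specific rates within a site are therefore generally well estimated, apart from sparse cells at small sites. The number of sites does not limit this step.

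**2. How a mix difference becomes a rate difference.** Let older veterans have rate *o* and younger veterans rate *y* (*assumed* equal in both groups of sites, so no funding effect), with shares of older veterans *m1* and *m2*.

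- Crude difference = (*m1* − *m2*) × (*o* − *y*).
- *Assumed* y = 5%, o = 10%, m1 = 55%, m2 = 50%: crude rates are 0.55 × 10 + 0.45 × 5 = 7.75% and 0.50 × 10 + 0.50 × 5 = 7.50%. The spurious difference is 0.25 points.
- *Assumed* y = 5%, o = 20%, m1 = 60%, m2 = 50%: 14.0% v 12.5%, or 1.5 points.
- Standardised to a common age mix, both differences are 0. This follows by construction, because age is the only confounder in the example; it does not show that standardisation would clear all case mix in the real data.

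**3. Aim 2 against site-level noise.** With a mean rate of 7.5% and an *assumed* log-scale site SD of 0.25, the site SD is about 7.5 × 0.25 = 1.9 points. For 23 v 12 sites the multiplier is √(1/23 + 1/12) = 0.356, so the standard error is about 0.67 points. A simulation on similar assumptions gave 0.7 to 0.9. The 0.25-point bias is about 0.3 to 0.4 of a standard error.

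How large a mix difference is plausible? By chance alone, the standardised difference of one covariate between 23 and 12 sites has a standard error of 0.356. With an *assumed* between-site SD of 6 points in the share of older veterans, that is 0.356 × 6 ≈ 2.1 points. A 5-point difference would therefore need more than ordinary chance, such as a systematic difference between the groups. Over standardised differences *d* of 0.36 to 1.0, between-site SDs *s* of 5 to 10 points and rate gaps *g* of 5 to 15 points, bias = *d* × *s* × *g*:

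- lowest: 0.36 × 0.05 × 0.05 = 0.09 points
- highest: 1.0 × 0.10 × 0.15 = 1.5 points

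No step named in aim 2 reduces this.

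**4. Aim 1 after matching.** If the 10% balance criterion is met, *d* ≤ 0.10. With the same ranges the residual bias from age is at most 0.1 × 0.05 × 0.05 = 0.025 to 0.1 × 0.10 × 0.15 = 0.15 points, against a simulated site-level standard error of about 0.5 to 0.6 points. The criterion may be missed. As a simple-random benchmark, the standard error of a standardised difference with 35 v 35 sites is √(2/35) = 0.24, and one covariate falls within 10% about 32% of the time. At *d* = 0.24 the bias is 0.06 to 0.36 points. This is residual imbalance in covariates that the plan already matches on and checks. The secondary Poisson model can adjust for it, although forward selection does not guarantee that demographics enter.

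**The case against.** The strongest reply is that aim 2 is described as a subgroup analysis and a comparative case study. It has no stated test, asks whether quantitative inference is possible at all, and openly discloses limited control of confounders. The article does not say how the rates are built, and a condensed article may leave that to a fuller document. The illustrative bias is also below one site-level standard error.

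Much of this stands, and it keeps the point modest. It does not dispose of it. The article does more than stay silent: it gives a reason for not controlling confounders, and that reason does not reach the measured patient demographics.

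Four stronger readings are tempting, and the documents do not support them.

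- *A reader might infer that aim 1 is a crude comparison too.* It is not. Sites are matched on a score that includes aggregate demographics, balance is checked for each covariate, fallbacks are named and a secondary model adjusts for site characteristics. AD completion is an aim 2 outcome only.
- *A reader might apply multi-point differences in age share to aim 1.* With a between-site SD of 6 points, shifts of 2.5, 5 and 10 points are standardised differences of about 42%, 83% and 167%, far outside the plan's 10% criterion.
- *A reader might note that the aim 1 z-test would call a tiny imbalance significant.* If it counts veterans, with 35 × 53,235 ≈ 1.86 million per group and a 10% rate, its standard error is about 0.03 points. That comes from ignoring clustering by site, which is a separate matter; standardisation would not cure it.
- *A reader might conclude that standardisation removes case mix.* It addresses only the demographics used. Illness, service use and other patient differences would remain, as would rurality and other site-level factors.

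**Conclusion.** The point holds for aim 2. The funded v unfunded contrast is planned without matching or adjustment, and the small number of sites explains only the lack of site-level control. The patient demographics extracted for the same aims allow each site's rates to be standardised at no cost in site-level degrees of freedom. For aim 1 only residual case-mix imbalance in the unadjusted primary z-test remains, after matching, balance checking and a secondary model that already remove much of it.

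The size of the bias is unknown, because the documents give neither rates by age nor the demographic mix of the two groups. The illustrations run from 0.09 to 1.5 points in aim 2, with 0.25 points as a worked example. These rest on assumed rate gaps, age shares and site variation, and on equal rates within strata. The change is worth making because it is cheap and bears on the main evaluation question, not because a large bias has been shown.

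**What to change.** In Data analysis for aim 2, state that funded and unfunded sites will be compared on site rates of ACP discussion and AD completion standardised for age, sex and race/ethnicity to a common veteran population. Use direct standardisation, or standardised rates from a patient-level logistic model where cells are sparse. Keep crude rates as descriptive.

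Reword the caveat so that the small number of sites is said to limit control of site-level confounders, and unmeasured confounders are acknowledged separately. Say that standardisation reduces confounding by the measured demographics, and that it does not address rurality. Do not say that case mix is removed.

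Optionally, use the same standardised site rates in the aim 1 comparison.

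The cost is a few sentences and some code on data already being extracted. The small downside is the modelling needed for sparse strata at small rural sites.
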